## Abstract

**Background:**

The COVID-19 pandemic has had major impacts in many different spheres, including mental health. Children and adolescents are especially vulnerable because their central nervous system is still in development and they have fewer coping resources than do adults. Increases in the prevalence of depressive and anxiety symptomatology have been reported worldwide. However, access to mental health care is limited, especially for the paediatric population and in low- and middle-income countries. Therefore, we developed a brief internet-delivered cognitive-behavioural intervention for children and adolescents with symptoms of anxiety and depression. The aim of this proposed study is to test the efficacy of the intervention.

**Methods:**

We will conduct a two-arm, parallel randomised controlled trial involving children and adolescents (8–11 and 12–17 years of age, respectively) with symptoms of anxiety, depression or both, according to the 25-item Revised Child Anxiety and Depression Scale (*t*-score > 70). A total of 280 participants will be randomised to the intervention group or the active control group, in a 1:1 ratio. Those in the intervention group will receive five weekly sessions of cognitive-behavioural therapy via teleconference. The sessions will focus on stress responses, family communication, diaphragmatic breathing, emotions, anger management, behavioural activation and cognitive restructuring. Participants in both groups will have access to 15 videos covering the same topics. Participant-guardian pairs will be expected to attend the sessions (intervention group), watch the videos (control group) or both (intervention group only). A blinded assessor will collect data on symptoms of anxiety, depression and irritability, at baseline, at the end of the intervention and 30 days thereafter. Adolescents with access to a smartphone will also be invited to participate in an ecological momentary assessment of emotional problems in the week before and the week after the intervention, as well as in passive data collection from existing smartphone sensors throughout the study.

**Discussion:**

Internet-delivered interventions play a major role in increasing access to mental health care. A brief, manualised, internet-delivered intervention might help children and adolescents with anxiety or depressive symptomatology, even outside the context of the COVID-19 pandemic.

**Trial registration:**

ClinicalTrials.gov NCT05139433. Registered prospectively in November 2021. Minor amendments made in July 2022.

## Administrative information

Note: the numbers in curly brackets in this protocol refer to SPIRIT checklist item numbers. The order of the items has been modified in order to group similar items (see http://www.equator-network.org/reporting-guidelines/spirit-2013-statement-defining-standard-protocol-items-for-clinical-trials/).

## Introduction

### Background and rationale {6a}

The coronavirus disease 2019 (COVID-19) pandemic has had major impacts on many different aspects of health, including mental health [1]. Because their brains are still in development, children could present short- and long-term physiological, cognitive and behavioural changes related to overly challenging situations such as those produced by the pandemic [2]. Their routine suffered major changes due to the restrictions imposed on school and leisure activities, leading to an increase in sedentary behaviours and screen exposure, as well as a decrease in the number of opportunities to socialise with their peers [3]. That could result in loneliness, which is associated with worse mental health outcomes and damages that can persist for years [4]. Financial losses and unemployment can increase the level of stress, as well as the frequency of anxiety, depression, substance abuse and violent behaviour, among parents, which can have an indirect effect on the mental health of the children and adolescents in the home [5, 6].

The emotional and behavioural effects that the pandemic has had on children and adolescents have been well documented [7–12]. Increases in the prevalence of depressive and anxiety symptomatology have been reported in various countries, including China [13, 14], Germany [10], India [8] and the USA [15], as have increases in hyperactivity, social conflict, conduct disturbances and other behavioural changes [7, 10].

Brazil is one of the countries most severely affected by the pandemic. In May 2021, over one in four COVID-19-related deaths occurred in Brazil [16]. It is also one of the countries in which schools were fully closed for an extended period of time [17]. It is estimated that approximately 4 million students dropped out of school during the pandemic in Brazil [18]. In a previous study conducted by our group [19], we found that, among children and adolescents in Brazil, one in three presented with clinical symptoms of anxiety or depression during the pandemic, and that number remained relatively stable from June 2020 to June 2021. In this context, it is vital to develop initiatives to mitigate the potential impact on this population. Some interventions have been shown to reduce the severity of the psychopathology related to traumatic events, such interventions including trauma-focused cognitive-behavioural therapy (CBT), prolonged exposure for post-traumatic stress disorder and cognitive therapy for post-traumatic stress disorder [20]. In the paediatric population, CBT is a well-established therapy for anxiety and depression [21]. In a meta-analysis, Kramer and Landolt [22] suggested that trauma-focused interventions for children and adolescents should include psychoeducation, teaching of coping skills, parental involvement and some form of trauma exposure. The current scenario, however, presents challenges and obstacles to the implementation of such therapeutic strategies. Brazil is a country of continental proportions, with many remote areas and a limited number of mental health professionals, most of whom reside in the major metropolitan areas [23]. A huge number of children and adolescents are now in need of mental health care, which was already difficult to access before the pandemic [24, 25]. During the pandemic, fear of contamination aggravated that scenario, as did the social distancing mandates and the temporary closure of some supporting services. Fortunately, online access to mental health services has now become more common [26]. Even though most studies of telemental health care have involved adult patients, it has been shown to be applicable in the paediatric population as well [27]. Therefore, telepsychotherapy could be a valuable tool during the COVID-19 pandemic and in other contexts in the future.

We developed a brief cognitive-behavioural intervention, to be delivered online, that is focused on anxiety and depressive symptomatology in children and adolescents. We aimed to craft a structured, user-friendly manual that will be freely available and can be followed by mental health professionals with limited experience and will therefore be disseminated throughout Brazil. Here, we describe the protocol for a randomised controlled trial designed to test the efficacy of this intervention.

### Objectives {7}

The objective of the proposed study is to test the efficacy of a brief cognitive-behavioural intervention to be implemented via teleconference (or telephone call) with a child or adolescent, together with a guardian. In a randomised controlled trial, the efficacy of the intervention will be compared with that of a video-based psychoeducational intervention (active control). We expect the active intervention to be the more effective in reducing emotional symptoms and in improving global functionality.

### Trial design {8}

We will conduct a single-blind, two-arm, parallel-group, superiority randomised controlled trial. Participants will be randomly allocated to the intervention group or to the active control group, in a 1:1 ratio.

## Methods: participants, interventions and outcomes

### Study setting {9}

Participants from all over Brazil will be able to participate remotely. The research centre is the Institute of Psychiatry of the Hospital das Clínicas, operated by the University of São Paulo School of Medicine, in the city of São Paulo, Brazil. The intervention will preferably be administered by videoconference. However, when that is not possible (due to internet connectivity issues or other problems), the sessions will be delivered by telephone.

### Eligibility criteria {10}

Children and adolescents with the following characteristics will be eligible to participate in the study: being between 8 and 17 years of age; living in Brazil; having a total *t*-score of ≥ 70 on the 25-item version of the Revised Children’s Anxiety and Depression Scale, parent report (RCADS-25-P) [28]; and having a total *t*-score ≥ 70 on the RCADS-25, child report (RCADS-25-C) [29]. The RCADS-25 measures the frequency of symptoms of anxiety and depression, using a 4-point Likert scale (“never”, “sometimes”, “often” or “always”), with subscale scores (for anxiety and depression, respectively) and an overall score. In an international consensus, the RCADS-25 was recommended as an outcome measure for anxiety and depression symptomatology in children and adolescents [30].

Participants will be excluded if there has been no contact between the child/adolescent and the guardian in the 15 days preceding the intervention; if there is not at least one parent/guardian participating in each session (intervention group) or available to watch the videos along with the child/adolescent (active control group); if the guardian is unable to understand the scales used in the assessments or the content of the interventions, according to the judgement of a clinical psychologist; or if the child/adolescent has previously been diagnosed with an autism spectrum disorder, schizophrenia or intellectual disability or has clinical signs of a severe mental disorder or social condition that requires more intensive assessment and treatment, such as severe mood disorder, suicide risk, intense intra-familiar conflict or intense maltreatment victimisation, according to the judgement of a clinical psychologist. Suicidality will be assessed with the aid of the parent-report four-item composite version of the Mood and Feelings Questionnaire for Suicidal Ideation (MFQ-SI) [31, 32], which comprises the following items (marked as “not true”, “sometimes true” or “true”, in relation to the last two weeks): “S/he thought that life wasn’t worth living”; “S/he thought about death or dying”; “S/he thought his/her family would be better off without him/her”; and “S/he thought about killing him/herself”. Children and adolescents whose parents marked the final statement as “true” or “sometimes true” will be excluded from the study and referred for appropriate care that is more intensive. Individuals who have been treated with any psychiatric medication or psychotherapy in the last 30 days will also be excluded.

### Who will take informed consent? {26a}

Parents who are interested in participating in the study will complete an online screening form. If their child is considered eligible in that initial assessment, a research manager will contact them by telephone to explain the study in detail and answer any questions they might have. The informed consent form (for the parent) and the informed assent form (for the child or adolescent) will then be sent, and a videoconference with an assessor will be scheduled, to confirm the eligibility criteria and perform the baseline (T0) evaluation. The forms will be collected at the beginning of this videoconference.

### Additional consent provisions for collection and use of participant data and biological specimens {26b}

Participants will be asked if they agree to allow their data to be used should they choose to withdraw from the trial. We will also ask their permission for the research team to share relevant data with other people at the University of São Paulo or at regulatory agencies, where relevant. This trial will not involve the collection of biological specimens.

## Interventions

### Explanation for the choice of comparators {6b}

Psychoeducational interventions consist of strategies to provide information and tools on how to better live and cope with a condition [33]. There is a growing body of literature on these kinds of interventions in mental health [33, 34], even within the paediatric population [34–36]. There is evidence that such interventions have beneficial effects, resulting in favourable mental health and well-being outcomes in adolescents with depressive symptoms [36]. The choice of a psychoeducational intervention as the comparator is therefore justified.

### Intervention description {11a}

#### Intervention group

We have developed a brief standardised, manualised cognitive-behavioural intervention for treating anxiety and depression in children and adolescents, to be implemented by trained psychologists via teleconference or telephone call. The main focus of the sessions will be skills training, with a CBT approach that employs vocabulary adapted to the target population. The psychotherapy programme will consist of five structured weekly sessions. The structure of each session is described in detail in the manual. Below is a brief description of the topics covered in each psychotherapy session.Session 1—The initial session covers the following: identification of the main symptoms and problems; psychoeducation on stress responses; strategies for improving communication within the family (e.g. defining minimal routines at home and how parents can listen to their child empathically); and relaxation and mindfulness techniques (diaphragmatic breathing exercises).Session 2—The second session focuses on emotion recognition and anger management. There is a psychoeducational component on emotions, covering the basic emotions of happiness, sadness, fear, disgust, surprise and anger, as well as their usefulness (e.g. motivating us to take necessary actions) and pitfalls (e.g. the potential for suffering). There is a greater emphasis on anger, exploring its physical, cognitive and behavioural components, and on strategies for coping with outbursts of anger, such as how they can be prevented and how to recover from one.Session 3—The third session focuses on behavioural activation, which is a technique based on the idea that avoidance behaviours exacerbate depressive symptoms. The technique is aimed at promoting adaptive behaviours that would be positively reinforced by scheduling potentially enjoyable and meaningful activities [37]. The rationale of behavioural activation is to stimulate participation. The therapist will guide the child/adolescent, with the help of a guardian, in creating a brief list of activities to be performed in the following week.Session 4—The aim of the fourth session is to teach the principles of cognitive restructuring. To that end, there is a psychoeducational component on what “thoughts” are, how to recognise them and the effects they might have on us, covering the basics of the cognitive model developed by Aaron T. Beck [38]. The last part of the session will focus on Socratic questioning [39].Session 5—The final session is aimed at revising any content of the previous sessions that was not clear to the family and providing a referral if necessary (e.g. to the public health care system if the child/adolescent is still symptomatic).

The first four sessions all have a homework component, encouraging the family to practice the strategies between sessions. Each session starts by reviewing the previous week’s homework. As the focus of the intervention is on skills building, the child/adolescent and the main guardian (preferably a parent) will both be required to participate in all sessions. It is expected that parent/guardian participation will improve learning because the adult should act as a model for the child/adolescent on how (and when) to employ the techniques learned. Some of the interventions are also focused on teaching the guardians new skills (such as establishing better routines at home and listening empathically to their child).

The intervention also comprises 15 psychoeducational videos that revise and deepen the content of the sessions. Families are expected (and encouraged) to watch the videos between sessions. The topics of each video are as follows:• Video 1—general information regarding the project and psychoeducation on stress responses• Video 2—parenting, communication and cooperation between family members• Video 3—diaphragmatic breathing• Video 4—a version of the diaphragmatic breathing video adapted for children• Video 5—progressive muscle relaxation• Video 6—mindfulness• Video 7—psychoeducation on emotions• Video 8—fear, sadness and anxiety• Video 9—coping with irritability• Video 10—behavioural activation• Video 11—establishing routines• Video 12—use of electronics by children and adolescents• Video 13—sleep hygiene• Video 14—cognitive restructuring• Video 15—coping with an anxiety attack

Each video is approximately 5 min in length. The families will have access to them via the COMVC smartphone application [40], which is available for Android and iOS. Videos will be made available according to the following schedule: first week, videos 1 to 6; second week, videos 7 to 9; third week, videos 10 to 13; and fourth week, videos 14 and 15.

#### Active control group

Children and adolescents in the active control group will receive a psychoeducational intervention that consists of the same 15 videos described above. The videos will be made available through the same smartphone application and on to the same schedule described for the intervention group.

### Criteria for discontinuing or modifying allocated interventions {11b}

Patients requiring a more intense type of treatment, such as individual psychotherapy or psychotropic medication, because of an increase in symptomatology (e.g. emergence of suicidal ideation), will be referred to the appropriate facility.

If a participant in the intervention group misses a session, the team will attempt to reschedule it, respecting the following criteria: no more than 4 weeks should elapse between the first and last session, and there should be at least 48 h between sessions, in order to allow families enough time to carry out the proposed homework. The fifth session can also be used to cover any topic that was missed because of participant inability to attend a previous session.

### Strategies to improve adherence to interventions {11c}

The intervention sessions will be recorded on video; 10% will be randomly selected to be watched by one of the authors of the manual, to assess therapist adherence to the protocol. Each session is described in detail in the manual, helping make the intervention more homogeneous among the various therapists of the research group. All of the therapists will receive weekly supervisory sessions led by senior psychotherapists. An assessor blinded to the allocation will register the percentage of psychoeducational videos watched by the patient and guardian.

### Relevant concomitant care permitted or prohibited during the trial {11d}

Participants who have, in the last 30 days, undergone any other form of psychotherapy or used any psychotropic medications will be excluded. However, those who present worsening of their symptoms during the intervention and require more intensive support (such as another form of psychotherapy and/or psychotropic medications) will be allowed to complete the protocol.

### Provisions for post-trial care {30}

Participants judged by the psychotherapist or the blinded assessor to be in need of further treatment after the end of the protocol will be referred to an appropriate facility within the Brazilian public health care system.

### Outcomes {12}

The primary outcome measure will be a change in the symptoms of anxiety and depression, as determined by the RCADS-25-P and RCADS-25-C [28, 29], between study entry (T0) and 1–3 days after the end of the intervention (T1, after five sessions of psychotherapy, five weeks of access to the psychoeducational videos, or both). The RCADS-25-P and RCADS-25-C will be completed by an independent clinician blinded to the allocation, on the basis of interviews (through videoconference or telephone call) with the guardians and the children/adolescents, respectively. The response variables will be the continuous T-scores for the three RCADS-25 domains (total, depression and anxiety).

Secondary outcomes will include the following: a change in the symptoms of anxiety and depression at follow-up; global functioning, assessed by the Clinical Global Impression (CGI) scale [41] and the Children’s Global Assessment Scale (CGAS) [30, 42]; the impact of mental health symptomatology, as determined with the Strengths and Difficulties Questionnaire (SDQ) impact supplement [43]; changes in irritability; emotional problems; environmental changes, as determined by passive smartphone data collection; the level of parental satisfaction with the telepsychotherapy sessions; and the potential harm (emergence of suicidal ideation and worsening of the quality of family relationships).

The blinded assessor will evaluate the difference between the anxiety and depressive symptomatology observed at T0 and that observed at follow-up (T2, 30 days after the last psychotherapy session, for the intervention group, or 30 days after the last video is made available, for the active control group) in an interview with the guardian and the child/adolescent, using the RCADS-25-P and RCADS-25-C.

The blinded assessor will evaluate the global functioning of the participants in interviews with the guardian and the child/adolescent (through videoconference or telephone call). The CGI-Severity (CGI-S) and CGAS scores obtained at T0 will be compared with those obtained at T1 and with those obtained at T2. Scores on the CGI-S range from 1 to 7, higher scores corresponding to greater symptom intensity. Scores on the CGAS range from 0 to 100, higher scores indicating better functionality. The CGI-Improvement (CGI-I) scores will be assessed at T1 and T2. Scores on the CGI-I range from 1 (“very much improved”) to 7 (“very much worse”).

The impact of the mental health symptomatology on the lives of the children/adolescents will be compared between T0 and T1, as well as between T0 and T2, by using the SDQ impact supplement [43], the score on which ranges from 0 to 10, higher scores indicating greater distress and impairment. The SDQ impact supplement will be completed by the blinded assessor in an interview with the guardian and the child/adolescent (through videoconference or telephone call).

Irritability is a quite common psychopathological trait in youth and is related to many disorders, including depression and anxiety [44]. Therefore, we will evaluate the changes in child/adolescent irritability, as reported by the parents/guardians, between T0 and T1, as well as between T0 and T2. To that end, the blinded assessor will apply the parent-report Affective Reactivity Index (ARI), an index created to assess irritability [45], in an interview (by videoconference or telephone call).

Participants ≥ 12 years of age with access to a smartphone will complete an ecological momentary assessment (EMA), which is a brief in-the-moment assessment of emotions, mood, stress and anxiety. Each of those participants will receive a notification on their smartphone to answer a series of questions intended to reflect their current state (“Right now, I feel…”), with a 7-point Likert scale ranging from 0 (“not at all”) to 7 (“very much”). The EMA employs the experience sampling method (ESM) schedule [46], which consists of 17 questions and takes 3 min or less to complete. The ESM schedule will be delivered at four random times every day, within four 3-h blocks from 9:00 to 21:00, for six consecutive days in the week prior to the trial period and in the week after its end.

Participants ≥ 12 years of age with access to a smartphone will be asked to install an application designed to passively collect data from the smartphone sensors—the passive remote measurement technology (pRMT) application from the Remote Assessment of Disease and Relapse (RADAR)-base platform [47]. The pRMT application will run in the background, requiring minimal input from participants, and will use the smartphone sensors to collect data on the following: ambient noise and light; relative GPS location (i.e. the distance travelled, rather than absolute coordinates or precise geographical location); the number of Bluetooth-enabled devices nearby; the duration of calls; the number of text messages and emails; the time spent using the smartphone; the time spent on social media; and battery life. Passive data collection will take place from T0 to T2. The aim of these measures is to determine whether parameters such as physical activity (estimated by the distance travelled) and proximity to other people (estimated by analysing Bluetooth connectivity with other smartphones) might be related to changes in anxiety and depressive symptomatology and whether those parameters show any improvement after the trial.

To assess the level of parental satisfaction with the telepsychotherapy sessions (intervention group only), parents will be asked to complete an adapted version of the Telemedicine Satisfaction Questionnaire (TSQ) [48].

Potential harms were defined as the emergence of suicidal ideation and worsening of the quality of family relationships. As previously mentioned, we will use the parent-report four-item MFQ-SI to assess suicidal ideation in the last 2 weeks [31, 32], comparing T1 with T2. The MFQ-SI will be completed by the blinded assessor in an interview with the guardian (through videoconference or telephone call). To identify worsening of the quality of family relationships in the last 2 weeks, we will use the family relationship subscale of the family impact module of the Pediatric Quality of Life Inventory (PedsQL) [49]. The PedsQL will be completed by the blinded assessor in interviews with the guardian at T0, T1 and T2. The family relationship subscale of the PedsQL comprises five items, covering topics such as “lack of communication between people in my family”. For each item, there is a 5-point Likert scale (responses ranging from “never” to “almost always”).

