### Sample size {14}

In a meta-analysis, Vigerland et al. [51] found the estimated size-effect for internet-delivered CBT in children and adolescents to be 0.62 (95% CI 0.41–0.84). Given that most of the studies assessed in that meta-analysis evaluated interventions involving a greater number of sessions than that to be evaluated in our study, we decided to be conservative and expect an effect size within the lower bound of that confidence interval, that is, 0.41. Therefore, the minimum sample size would be 190 participants, with an alpha of 0.05, power of 80% and 1:1 randomisation. Assuming an estimated attrition rate of 30%, we will need a total sample of 280 participants.

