## Statistical methods

### Statistical methods for primary and secondary outcomes {20a}

We will use generalised linear mixed models (GLMMs) to analyse the effects of the intervention. The primary outcome will be the change, from T0 to T1, in the total scores on the RCADS-25-P and RCADS-25-C. Fixed and random effects will be modelled with GLMMs. The fixed effects will be the randomisation status (intervention group vs. active comparator group) as an independent variable, along with the potential confounders (age, sex and other baseline characteristics). The random effect will be on the subject (first) level. Time will be inserted as a continuous independent variable. We will use the intention-to-treat approach—all randomised subjects will be included in the analysis, even if they drop out or switch arms. The marginal means of the models will be extracted by randomisation status and time, after which they will be plotted in a time series. In a second step, we will analyse the effects that the intervention has on the symptoms of depression and anxiety in the children and adolescents. For all models, we will present the beta coefficients with a confidence interval of 95%. For all statistical tests, the level of significance will be set at 5%. Analyses will be performed with the Stata software package, version 16.0 (StataCorp, College Station, TX, USA), and the programme R, version 4.0.1 (The R Foundation for Statistical Computing, Vienna, Austria).

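### The primary outcome is defined in two ways, and even the narrower definition tests two unranked totals at 5% with no success rule, so the stated pair of alpha 0.05 and 80% power is not assured

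*Protocol article*

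**What the plan says.** Four places in the protocol article bear on this.

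- **Outcomes {12}.** The primary outcome is the T0-to-T1 change in anxiety and depression symptoms "as determined by the RCADS-25-P and RCADS-25-C". The section then adds: "The response variables will be the continuous T-scores for the three RCADS-25 domains (total, depression and anxiety"). Three scores on two informant forms make six variables.
- **Statistical methods {20a}.** "The primary outcome will be the change, from T0 to T1, in the total scores on the RCADS-25-P and RCADS-25-C". That is two variables, here called total scores rather than T-scores. The other domains follow later: "In a second step, we will analyse the effects that the intervention has on the symptoms of depression and anxiety". On error control the section says "For all statistical tests, the level of significance will be set at 5" per cent.
- **Sample size {14}.** The authors "expect an effect size within the lower bound of that confidence interval, that is, 0.41", and conclude: "Therefore, the minimum sample size would be 190 participants, with an alpha of 0.05, power of 80% and 1:1 randomisation". Allowing for 30% attrition, they plan 280.
- **Trial status.** Amendments registered in July 2022 reduced the number of primary outcomes. The section does not list those that were kept.

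No section names a lead informant, combines the two informants, or states how many scores must be significant for efficacy to be claimed.

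**The concern.** Two sections give different lists of primary variables, and both cannot be the primary outcome. Under either list there is more than one primary test, each at 5%, while the sample size rests on one.

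What the trial guarantees then depends on a rule that is not written down. If a significant result on any one score counts as success, the chance of a false claim exceeds 5%. If every score must be significant, the chance of success under the assumed effect is below 80%. Parent and child reports may disagree, and one domain may move without the other. In those cases the text would let the claim be chosen after the results are known.

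**Working it through.** **Inputs from the document.** d = 0.41 (SD = 1), alpha 0.05, power 80%, 1:1 allocation, 190 evaluable, 280 randomised, 30% attrition. Sidedness is not stated; the two-sided test is the one that reproduces 190 (one-sided gives 148).

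**Assumptions.** The document gives no correlation between scores, so a range is used. The effect is taken as 0.41 on every score.

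**1. Reproduce the stated size.** Normal formula: n per arm = 2(1.960 + 0.842)² / 0.41² = 93.4, so 94 per arm. The t-test needs 94.35, so 95 per arm and **190 in total**, an exact match. With attrition, 190 / 0.70 = 271.4, so 272; the planned 280 covers this and leaves 280 × 0.70 = 196 evaluable (98 per arm). Power for one test is 0.803 at 190 and 0.815 at 196 (t-test), or 0.807 and 0.819 (normal). The arithmetic is right for one endpoint.

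**2. Two totals, each at 5%.** The test statistics have mean 0.41 × √(N/4), which is 2.826 at N = 190 and 2.870 at N = 196. They are treated as bivariate normal with correlation r.

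- Family-wise error (either suffices) = 1 − P(both |Z| ≤ 1.960). At r = 0 this is 1 − 0.95² = 9.75%.
- Power (both required) = P(Z₁ > 1.960 and Z₂ > 1.960).
- Power (either suffices) = 2 × single-test power − power for both. Example at N = 190, r = 0.5: 2 × 0.807 − 0.697 = 0.917.

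| r | Family-wise error, either | Power, either (N = 190 / 196) | Power, both (N = 190 / 196) |
|---|---|---|---|
| 0.3 | 9.5% | 93.8% / 94.4% | 67.6% / 69.3% |
| 0.5 | 9.1% | 91.7% / 92.5% | 69.7% / 71.4% |
| 0.8 | 7.8% | 87.6% / 88.5% | 73.7% / 75.2% |

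These use the normal approximation. The t-distribution lowers power by roughly half a point (as in 0.807 against 0.803 above), so power for both at r = 0.3–0.5 is about 67–71%.

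**3. Six scores, each at 5%.** Two assumed correlation patterns were simulated.

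- Within one informant, 0.65 (depression–anxiety), 0.85 (total–depression) and 0.93 (total–anxiety), multiplied by 0.2 to 0.7 across informants: family-wise error 17.2% falling to 14.9%.
- All six equally correlated at 0.3 to 0.8: family-wise error 24.3% falling to 14.0%.

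The range for an any-score rule is therefore about 14–24%. If all six had to be significant, power would be about 41–64%.

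**4. Holm across the two totals.** The smaller p-value is tested at 2.5% (critical value 2.241), and the other at 5% if the first passes.

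- At least one = 2P(Z > 2.241) − P(both > 2.241).
- Both = 2P(Z₁ > 1.960, Z₂ > 2.241) − P(both > 2.241).
- Per informant = the average of those two.

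At N = 190, r = 0.5: 85.9%, 68.6%, and (85.9 + 68.6)/2 = 77.2%. At N = 196, r = 0.3: 89.6%, 68.5%, and 79.0%. Over r = 0.3–0.5 and 95–98 per arm, after the half-point t correction: about 77–79% per informant, 85–89% for at least one, and 66–70% for both.

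**The case against.** The best defence is that the Statistical methods section governs. It names the two totals and puts depression and anxiety in a later step, so the Outcomes section may only be listing every score to be modelled. The July 2022 reduction fits that narrower set. Hierarchy between informants is also the kind of detail often left to an analysis plan, which is not shown. And since no success rule is stated, neither inflated alpha nor lost power is established.

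Much of this stands. The two-total reading is the more natural one and should carry the weight; the six-score figures apply only if the Outcomes section is taken at its word. But the Outcomes section attaches all three domains to the primary outcome, and Trial status does not say which outcomes survived, so the text does not settle the matter. An analysis plan could not settle it either without overriding one section, and any multiplicity adjustment would depart from the 5% fixed for every test.

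A reader might infer more than the document supports:

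- **That alpha and power both fail.** They do not fail together. An either-total rule inflates alpha while power stays above 80%; a both-totals rule keeps alpha at or below 5% and lowers power.
- **That the sample size is miscalculated.** It is correct for one test.
- **That six tests at 5% mean an error of 1 − 0.95⁶ = 26.5%.** That needs independent scores, which is impossible when each total contains its own depression and anxiety items.

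It is also fair to say that a single named informant is not the only valid choice. Eligibility requires a high score on both forms, which suggests the sponsor may value the two informants equally.

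**Conclusion.** The point holds as an inconsistency plus an incomplete decision rule. The two sections disagree on the primary outcome, and under either version the documents do not assure 5% error and 80% power together. The primary claim needs one definition, fixed before results are seen.

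Under the narrower reading the size is moderate: an error of about 9–9.5% if either total suffices, or power of about 67–71% if both must be significant (7.8% and about 73–75% at r = 0.8). Under the six-score reading with an any-score rule, the error is about 14–24%. All of these rest on assumed correlations, and the power figures also assume an effect of 0.41 on each form. The existence of the problem does not depend on those assumptions; only its size does.

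**What to change.** Amend Outcomes {12} and Statistical methods {20a} so that they agree:

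1. Make the change in RCADS-25 total T-score from T0 to T1 the only primary variable, and use the term T-score in both sections.
2. Make the depression and anxiety T-scores secondary.
3. Name one informant's total as primary before results are seen.
4. Test the other informant's total at 5% only if the first is significant.

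Alpha then stays at 5% across the two totals, and the 190/280 and 80% power stand for the first test. The cost is wording in the protocol, registry and analysis plan before database lock; the downside is that the second informant's test becomes conditional.

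If the sponsor wants the informants on equal footing, there are two options:

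- **Holm across the two totals.** State power as about 77–79% per informant, 85–89% for at least one and 66–70% for both (d = 0.41 on each form, r = 0.3–0.5, 95–98 per arm). A figure near 73% would be wrong here: it is the Bonferroni power for one named endpoint at 2.5%.
- **Both totals required at 5% each.** No alpha adjustment is needed, but power should be restated as about 67–71%. Keeping 80% would take 240 evaluable at r = 0.3 or 234 at r = 0.5, that is 240/0.70 = 343 or 234/0.70 = 335 randomised.

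Trial status should also state which primary outcomes the July 2022 amendment kept.
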